**Methods:**

This 3-arm, parallel design, double-blind, randomized controlled trial involves 791 preschool children. Children are randomly allocated to receive 1 of 3 interventions as follows: Group 1, 38% SDF; Group 2, 5% NaF varnish; and Group 3, placebo control (tonic water). The intervention and dental examination will be carried out every 6 months. A parent-administered questionnaire, including the children’s demographic background and oral health–related behaviors, has been collected at baseline. Follow-up examinations to detect new caries development will be conducted every 6 months by a masked examiner. Caries development will be diagnosed at the cavitation level. Chi-square tests and logistic regression analyses will be adopted. A 2-level logistic regression analysis will be performed to investigate the effects of the study interventions and other potential confounding factors on the development of occlusal caries.

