### Questionnaire Survey

A parental questionnaire consisting of 3 fields (child’s information, child’s oral health–related behavior, and family information) will be administered at baseline and at the 30-month follow-up visit. It will collect information regarding the child’s oral hygiene practice, use of fluoride agents, dental visit behavior, snacking habits, parental educational level, and family income. The questionnaire will also assess parental satisfaction with their child’s oral health and dental esthetics. In the follow-up questionnaire, parents will be asked to report posttreatment complications of the assigned treatment, such as pain from the treated teeth and gingival irritation around the treated teeth.

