A chi-square test and *t* test will be performed, when appropriate, to assess the differences between groups with regard to their baseline demographic background, oral health–related behaviors, and caries experience. A chi-square test will be used to evaluate the differences in new caries development and parental satisfaction among groups. Thus, 2-level generalized estimating equation models with a logit link function (child level and surface level) will be adopted to evaluate the variables influencing the occurrence of occlusal caries at the 30-month follow-up. Independent variables include the child’s background characteristics (gender, place of birth, father’s and mother’s education levels, and family income); the child’s clinical characteristics at baseline (tooth type, such as upper or lower molars and first or second molars, presence of plaque on the occlusal surface, caries experience, and overall oral hygiene); and the child’s oral health–related behaviors (use of fluoride agents, dental visit behavior, and snacking habit). The backward elimination method will be adopted for modeling. A McNemar test will be performed to compare the differences in parent’s satisfaction with their child’s dental appearance and dental health at baseline and the 30-month follow-up. The level of statistical significance for all tests will be set at .05. An intention-to-treat (ITT) analysis will be adopted so that all study children who are randomized and all events will be accounted for in the primary analysis. The relevant government agencies have access to the collected data for the purposes of verifying the integrity of the study data and evaluating compliance with the study protocol. Regarding confidentiality, hard copies of the data will be stored in a sealed box in a locked room during the trial and after publication for 5 years. In addition, the research findings will be presented in scientific conferences for clinicians and health care researchers, and will be disseminated to the community and stakeholders through oral health educational seminars and talks.

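### The only clustering-aware arm comparison starts from about seven parent-questionnaire covariates and is cut by backward elimination, which fits the all-randomised-children promise only if blank answers are imputed or coded

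*Protocol article*

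**What the plan says.** All references are to the protocol article.

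- **Data Analysis, covariates.** The 2-level GEE with a logit link lists among its independent variables "gender, place of birth, father’s and mother’s education levels, and family income" and "use of fluoride agents, dental visit behavior, and snacking habit". It also lists clinical items recorded by the examiner, such as tooth type and occlusal plaque. The model is then reduced by backward elimination.
- **Questionnaire Survey.** The form is described as "A parental questionnaire consisting of 3 fields" and collects, among other things, "use of fluoride agents, dental visit behavior, snacking habits, parental educational level, and family income". It "will be administered at baseline and at the 30-month follow-up visit".
- **Abstract, Methods.** The 2-level regression is meant "to investigate the effects of the study interventions and other potential confounding factors on the development of occlusal caries". I read this as the same model as the GEE. It therefore serves both as treatment comparison and as risk-factor search.
- **Data Analysis, other comparison.** A chi-square test of new caries among groups is also named. It uses no covariates.
- **Data Analysis, ITT.** The section promises that "all study children who are randomized and all events will be accounted for in the primary analysis". It does not say whether the chi-square test or the GEE is that primary analysis.

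**The concern.** A GEE cannot use a record with a blank covariate unless the blank is imputed or given its own category. With questionnaire items in the starting model, a child whose parent skipped one answer can be left out with all of his or her surfaces, although the examiner recorded the outcome. This loss is separate from the planned 20% dropout, because these children were followed.

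Backward elimination adds a second problem. The first decisions about which items leave would be made only in children complete on every item. As items go, children can re-enter, so successive models may describe different sets of children.

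At stake are the precision of the arm comparison and how well the analysed children represent those randomised. Family income and both parents' education are not needed for an unbiased comparison in a randomised trial, so any loss they cause buys no protection against confounding.

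**Working it through.** **1. Count of items.** Background: gender, place of birth, father's education, mother's education, family income (5). Behaviours: fluoride use, dental visits, snacking (3). That is 8, or 7 if gender is not counted as a questionnaire item. I use 7. The article names the form as the source of education, income and behaviours. For place of birth the source is inferred from the form's field on the child.

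**2. The plan's own sample size.** Inputs from Sample Size Calculation: 25% against 15%, two-sided 5%, power 90%, ICC 0.5, 6 surfaces per child, 20% dropout.
- Fisher exact power is 0.8995 at 350 surfaces per group and 0.9004 at 351, so the stated 351 is reproduced.
- Design effect: 1 + (6 − 1) × 0.5 = 3.5.
- 351 × 3.5 = 1228.5, about 1229 surfaces. 1229/6 = 204.8, about 205 children per group, and 205 × 3 = 615.
- 615/0.80 = 768.75, about 769.

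All stated figures reproduce, and this point does not affect them.

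**3. Margin.** With 791 enrolled (Results), 791 × 0.80 = 632.8, about 633 followed. Against 615 needed, the spare fraction is 1 − 615/632.8 = 2.8%.

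**4. Loss if incomplete children are left out.** The documents give no blank rate, so the rate q per item is an assumption.
- Independent blanks: fraction kept = (1 − q)^7.
- Fully overlapping blanks (the same children skip everything): fraction kept = 1 − q.

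**5. Power.** Effective surfaces per arm: n = (children/3) × 6/3.5. Pooled two-proportion test: power = Φ{[0.10√n − 1.96√(2 × 0.20 × 0.80)] / √(0.25 × 0.75 + 0.15 × 0.85)}. With no loss, n = 361.6 and power = 0.921.

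| Assumed q | Independent: kept | Children left of 633 (lost) | Power | Overlapping: children left | Power |
|---|---|---|---|---|---|
| 0.5% | 96.6% | 611 (22) | 0.912 | 630 | 0.920 |
| 1% | 93.2% | 590 (43) | 0.902 | 626 | 0.919 |
| 2% | 86.8% | 549 (84) | 0.881 | 620 | 0.916 |
| 5% | 69.8% | 442 (191) | 0.804 | 601 | 0.908 |
| 10% | 47.8% | 303 (330) | 0.643 | 570 | 0.892 |

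The pooled test is slightly more optimistic than the exact test behind 351 (it gives 0.914 at 615 children). That is why 590 children still reach 0.90.

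**The case against.** **Deletion is not stated.** Nothing in the article says that children with a blank are removed. Complete-case fitting is inferred from usual software behaviour, and a missing-covariate rule is commonly left to an analysis plan or full protocol that is not shown. This stands. A reader might infer that the article contradicts its ITT statement outright, but the documents do not support that. They show a model and a promise that fit together only with a step the article does not mention. What remains open to criticism is the stated choice of covariates and selection method for a model that also carries the arm effect.

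**The ITT promise may refer to the chi-square test.** The article does not tie the promise to the GEE, and the chi-square test loses no child to a blank form. True, but a surface-level chi-square test ignores the clustering for which the trial itself assumes a design effect of 3.5. Data Analysis says multilevel analysis is needed for that reason.

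**Elimination may drop the items.** It may, so a blank need not exclude a child from the final model. The elimination path would still start in the complete subset.

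**Bias between arms.** A reader might infer that the randomised comparison is broken. The documents do not support that: the Abstract says the form was collected at baseline, and parents were not told the allocation. Leaving children out on baseline completeness keeps the arms comparable in expectation.

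**Unavoidable blanks.** A reader might also infer that asking for both parents' education forces a blank where one parent gives no answer. The form is not shown and could offer a not-applicable option, so this cannot be claimed.

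**Adjustment can help.** Covariate-adjusted arm effects are legitimate in a randomised trial, and the power figures above credit no precision gained from prognostic covariates. This also stands.

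**Conclusion.** The point holds as a conditional risk that is cheap to remove. The only clustering-aware arm comparison rests on about seven parent-reported covariates and a data-driven selection step. Without imputation or coding of blanks, it would not include all followed children.

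The size cannot be derived from the documents. Under independent blanks of 1% to 5% per item, about 43 to 191 of 633 followed children are lost and power is 0.90 to 0.80, against 0.92 with no loss. Independence is the unfavourable case: with full overlap at the same rates, power stays at about 0.91 or above, and even independent blanks of 1% still meet the 90% target.

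The harm is mainly to precision and representativeness. That judgement assumes the baseline answers are used. The form is also given at 30 months, and the article does not say which occasion supplies the behaviour items.

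**What to change.** In Data Analysis, name as the primary arm comparison a GEE with prespecified terms that are not subject to elimination: arm, the randomisation stratum (baseline dmfs 0 against >0, from the random allocation section) and examiner-recorded baseline items (tooth type, occlusal plaque). None of these depends on the parents' form, so the comparison fits the ITT statement without a rule for blank answers.

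Keep the questionnaire items and backward elimination for a separate risk-factor model, and state that the treatment effect is not taken from it.

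The cost is a change of wording and one extra model, with no new data. The arm effect would not be adjusted for socioeconomic items, so any precision they would have added is given up.

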## Results

This study was started on September 1, 2020, and the recruitment process ended on September 30, 2021. At present, a total of 791 children are participating in the study. This 30-month clinical trial is expected to be completed in March 2024.

## Discussion

This is a randomized, 3-arm, double-blind, parallel-design clinical trial that aims to investigate the effectiveness of semiannual application of 38% SDF, 5% NaF varnish, and placebo for preventing new caries on occlusal surfaces of primary molars. We hypothesize that SDF has a better effect for preventing occlusal caries than NaF varnish and control owing to its promising results in remineralizing initial enamel caries lesions [23]. The caries-arresting effects of SDF in preschool children have been well documented. However, there is limited information on the effectiveness of SDF for primary prevention purposes in young children. The effect of SDF on caries in primary teeth was systematically reviewed [20,24]. Unfortunately, all included studies in the meta-analysis primarily focused on therapeutic effect, and SDF was applied to decayed teeth. So far, there is insufficient evidence regarding the preventive effect of SDF in primary teeth in vivo. Therefore, it is essential to investigate the caries-preventive effects of SDF versus NaF varnish and placebo control on the occlusal surfaces of the primary molars of preschool children. It should be noted that the children in the placebo group will not receive substandard care, since there are no existing government subsidized programs that provide professionally applied topical fluorides to prevent dental caries in kindergarten children. In fact, all participant children will have additional benefits from regular dental check-ups and receive a free toothpaste and toothbrush. Parents of the study children will receive oral health information through distributed leaflets and oral health seminars in the kindergarten.

Preventing the development of ECC is the ultimate goal of a disease management plan. Based on recent epidemiological studies, ECC remains prevalent globally [25], and the situation is more challenging in low-income countries [26]. An innovative evidence-based preventive program is needed. Since the proposed caries prevention protocol is feasible, affordable, and noninvasive, if shown to be effective, it can be adopted in a school-based or community-based setting to prevent ECC in children from disadvantaged communities. The strength of this study is adequate sample size, thus leading to sufficient study power. A limitation of this study is that the results of this trial conducted in healthy young children may not be translatable to other groups of children who have special health care needs or other age groups. A further study on the preventive effect of SDF conducted in patients with special health care needs is required. We plan to disseminate the research findings to different audiences as follows: (1) For dental practitioners and dental educators, the research findings will be published in international peer-reviewed journals and presented at scientific conferences; (2) For community health care teams, kindergarten teachers, and stakeholders, workshops about caries prevention for preschool children will be arranged in Hong Kong; and (3) For end users (children and parents), a story and brief summary of the research findings will be presented in plain language through newsletters and videos on the faculty website, as well as local multimedia.

The results of this study will provide evidence to strengthen or refute the recommendation regarding the use of SDF for preventing occlusal caries in primary molars. The study findings can guide decision-making among dental practitioners and health policymakers regarding whether SDF should be included in a school-based caries prevention program.

## Appendix

Multimedia Appendix 1 SPIRIT (Standard Protocol Items: Recommendations for Interventional Trials) checklist.

## Abbreviations

dmfs: decayed, missing, and filled tooth surface
ECC: early childhood caries
NaF: sodium fluoride
SDF: silver diamine fluoride
